### Interventions

All groups will receive current standard of care physical therapy from a licensed physical therapist. Physical therapy sessions will consist of typical standard of care treatment followed by BFRT or sham BFRT. The standard of care portion of the session will consist of brief subjective and objective screening followed by a structured treatment paradigm consisting of pain modulation, neuromuscular re-education, dynamic warm-up, range of motion and mobility, progressive strengthening, and power training with an emphasis on the lower extremities and trunk musculature. The standard physical therapy portion of the treatment session will last approximately 40 min. Interventions for pain modulation, range of motion, and neuromuscular re-education, balance, and gait training will be utilized as needed to address individual subjects’ specific needs at the time of screening based on the severity of the injury and with the goal of adequately preparing them to return to their sport of choice.

### Blood flow restriction training

Two brands of blood flow restriction units will be used (brand names not included in this text to avoid the potential for subjects to become unblinded). Subjects will be split into groups as previously described where brand 1 will be used as sham BFRT and the intervention group will use brand 2. All quadriceps-focused exercises will be performed with the bands inflated. As directed by the manufacturer’s instructions, the bands will be placed on the proximal thigh as close to the femoroacetabular joint as possible (Fig. 1). Limb arterial occlusion pressure will be constantly monitored and adjusted by the unit to maintain the desired occlusion pressure throughout the duration of exercise. Consistent with our current trial assessing the efficacy of BFRT for ACL reconstruction patients (NCT03364647), participants in all groups will perform the same exercises with an emphasis on quadriceps and hip strengthening, and for those randomized to the active BFRT groups, each BFRT session will last approximately 20 min [12]. All subjects will attend 3 visits per week for 8 weeks divided in to 4 phases.

**Fig. 1 Fig1:**
[figure not shown]
Blood flow restriction training cuff placement. The BFRT band is applied to the upper thigh of the subject’s leg. Pressure is continuously regulated by the controller unit during training

The active BFRT group will have the arterial blood flow occlusion pressure set per manufacturer instructions to achieve the desired limb occlusion pressure (LOP), whereas the sham BFRT group will have restriction pressure set at a sub-clinical level of occlusion. Occlusion personalized tourniquet pressure (PTP) will be reassessed each visit by rechecking the LOP. Each subject will perform a block of 4–5 quadriceps and hip-focused exercises each lasting approximately 5 min for a total of 20 min (exercises: seated single leg press, seated single leg knee extension, single leg forward step-ups progressed to forward step downs when tolerated, and resisted double leg squats). Exercise intensity will be adjusted between groups to accommodate the achievement of volitional fatigue and an acceptable sensation of discomfort during exercise. Cuffs will be deflated for a minimum of 1 min between exercises. The quadriceps and hip strengthening exercises with the cuff donned will be performed at the end of the rehabilitation session with the intention of reducing the impact of fatiguing the muscles for the standard physical therapy portion of the treatment session.

For all subjects, rating of perceived discomfort and rating of perceived effort will be recorded from separate 11-point Likert-type scale (0 no discomfort or effort to 10 maximal discomfort or effort) for each BFRT exercise. Emphasis will be placed on distinguishing between effort (the amount of physical energy being given to the exercise) and discomfort (the physiological and unpleasant sensations associated with the exercise), with the goal of maximizing effort. All exercises should be challenging and/or hard to perform; however, subjects need to maintain proper form, as determined by the treating physical therapist, to ensure appropriate quadriceps engagement.

Criteria for progression of resistance or exercises include (1) no excessively aberrant movement causing pain due to fatigue of desired muscle group(s), (2) no excessive form deviation where the desired muscle group is no longer the primary mover completing the desired task, (3) no concordant pain > 4/10, (4) ability to complete delineated sets and repetitions without pausing within a set, and (5) able to complete 2 or more repetitions than delineated during the last set of the exercise.

Criteria for clearance to return to sport include (1) negative moving patellar apprehension test, (2) a score of 0 indicating no effusion with the stroke test, (3) at least 0 degrees of knee extension active range of motion of the involved knee, (4) knee flexion active range of motion within 5 degrees of the uninvolved knee, (5) < 4/10 numeric pain rating with activity, and (6) 90% limb symmetry index as measured with isometric knee extension peak torque and the 60-s step down test.

### Treatment adherence

Treatment adherence is the extent to which a therapist uses interventions prescribed by a protocol. To maximize adherence and treatment fidelity, electronic logs of all the exercises per session will be kept on a custom Microsoft Access database. Adherence to the treatment protocol will be audited by an external physical therapist regularly throughout the duration of the study. We will monitor session attendance using a diary log with participant ID numbers and session dates to track the percentage of attendance and to account for absenteeism and reasons for missed sessions. We will make every effort to deliver the full treatment, but we expect some variation in treatment delivery dose as well as treatment drop-out. Reasons for attrition will be assessed with an open-ended question for enrolled participants who withdraw.

### Outcome measures

Primary outcomes include the Norwich Patellar Instability Scale [13] collected at the time of enrollment, 4 weeks, 9 weeks, 6 months, and 12 months after enrollment, isometric and isokinetic quadriceps strength at 1 week, 4 weeks, 9 weeks, 6 months, and 12 months after enrollment, MRI T1ρ and T2 relaxation times 1 week, and 12 months enrollment, and biochemical biomarkers which will include urinary C-terminal cross-linked telopeptide type II collagen (CTXII) and a neoepitope of type I and type II collagen cleavage (C1,2C) at the time of enrollment, 4 weeks, 9 weeks, 6 months, and 12 months after enrollment. Secondary outcomes include the VAS for pain [14], Cincinnati Occupational Rating Scale [15], Tegner Activity Scale [16], and the time to returning to work and/or sporting activities, hip muscle strength (hip abduction, hip external rotation), and knee biomechanics (knee extensor moment, knee flexion excursion, knee adduction moment, knee adduction excursion) during walking, running, and anterior step-downs 1 week, 9 weeks, 6 months, and 12 months after enrollment. Data will be captured using REDCap and will be reviewed on a quarterly basis by an unblinded member of the study team to ensure data quality and completeness (Table 2).

**Table 2 Tab2:**
[figure not shown]
Flowchart of study activities

### Statistical methods

The primary outcome variable for Aim 1 is the Norwich Patellar Instability Scale. Utilizing the standard deviation of 18.6 points from our pilot results, a sample size of 34 subjects per group will be adequately powered (80%) to detect a moderate effect size between groups difference (13 points difference, effect size = 0.7). To protect against up to 15% of subjects being lost to follow-up, an additional 5 subjects will be enrolled per group (39 subjects per group; 78 total). Based on our previous pilot work, a sample size of 34 patients per group will also be more than 80% powered to detect group differences in the primary outcome variables for both Aim 2 (quadriceps strength and knee biomechanics) and Aim 3 (T1ρ relaxation time).

Since all endpoints are quantitative and longitudinal data is collected, repeated measures analysis of covariance (ANCOVAs) will be used to assess differences in scales across the two treatment groups (BFRT vs. sham BFRT). The repeated measures ANCOVAs will adjust for demographic covariates (e.g., age, sex, and race) as well as look for differences across any other potential confounders (such as first-time vs. repeated instability events). Assumptions such as normality and constant variance will be assessed, and remedial measures will be employed as needed. In addition, interaction effects and/or variable transformations will be explored appropriately. In the case that endpoints are related, multivariate analysis of covariance (MANCOVAs) may be used to consider those that naturally group themselves.

All analyses will be performed with a significance level of 0.05, and appropriate multiple comparisons adjustments will be performed as needed. Categorical variables will be described with counts and percentages and analyzed using appropriate statistical methods, such as hypothesis tests or logistic regression models.

For both primary and secondary analyses, in the case of participants that violate group allocation or do not attend a minimum of 80% of the prescribed physical therapy sessions, we will perform intention-to-treat and per protocol analyses. We will not employ imputation methods in the case of missing data. No interim or other subgroup analyses will be performed.

Participant information will be combined with information from other people taking part in the study. When we write about the study to share it with other researchers, we will write about the combined information we have gathered. Participants will not be personally identified in these written materials. We may publish the results of this study; however, we will keep participant names and other identifying information private. The study information collected from participation in the study may be entered into a secure computer system. The study physician is committed to maintaining the privacy of every study participant and any personal information submitted and follows the principles of the Health Insurance Portability and Accountability Act (HIPAA) of 1996. All data are stored at a secure site behind a firewall, which monitors and protects against unauthorized access. Participant charts and any other items containing confidential items will be stored in a safe place overnight and not left on the desk. Charts will not be left in an area where others might have access to them. Participants should know, however, that there are some circumstances in which we may have to show their information to other people. For example, the law may require us to show their information to a court or to tell authorities if they report information about a child being abused or if they pose a danger to themselves or someone else. Officials of the University of Kentucky, the Department of Defense, members of an independent Data Safety Monitor Board, the Center for Clinical and Translational Science, and Bluegrass Research Consultants may look at or copy pertinent portions of records that identify participants. Participants withdraw from the study or are withdrawn; data collected to that point will be kept.

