## Background

Patellar dislocations are a common and understudied condition that disproportionally affects athletes and military personnel [1]. The rate of having a patellar dislocation is greater than having an anterior cruciate ligament (ACL) tear in this population [1]. Regardless of intervention, 30% to 50% of those who sustain a primary dislocation experience continued pain and the sensation of instability [2]. A significant long-term concern is the rate of post-traumatic osteoarthritis that develops following a patellar dislocation which can be up to 50% of individuals within 5–15 years after injury [3]. Nonoperative treatment is currently the standard of care following most first-time dislocations; however, 31% of patellar instability patients treated conservatively suffer a re-dislocation [4]. A single patellar dislocation increases the lifetime risk of post-traumatic osteoarthritis (PTOA) and recurrent dislocations markedly increase this risk [3, 5]. Therefore, there is an urgent need to minimize the incidents of recurrent patellar dislocations and PTOA sequela which safely allows an earlier return to sport or work while also limiting long-term functional impairments and reduced quality of life.

While nonoperative treatment is most commonly employed for patellar instability, specific evidence-informed rehabilitation guidelines are sparse [4]. One modality that could potentially improve treatment for those with patellar instability is blood flow restriction training (BFRT). BFRT involves the use of an inflatable cuff applied to the thigh to slow arterial blood flow and eliminate venous return as subjects exercise with a relatively low resistance. It is thought that the increased metabolic stress and mechanical tension during BFRT act to stimulate various metabolic pathways leading to muscle hypertrophy [6–8]. There is evidence supporting the premise that BFRT will result in improved quadriceps and hip strength without the need for high-intensity resistance exercise [9–11]. Due to the nature of patellar instability, patients may not tolerate high-intensity quadriceps exercises early in the rehabilitation process thus delaying the recovery of strength. BFRT may allow them to receive the same training benefits as if they were training under high loads. Achieving greater muscle strength earlier after injury may result in improved lower extremity biomechanics, improved functional capacity, and an accelerated recovery.

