## Methods/design

### Aims

The overarching rationale is that BFRT will expedite the return to work or sports, minimize muscle impairment, and ultimately slow cartilage degradation over the first year following patellar dislocation. This strategy will improve patient-reported outcomes and accelerate restoration of symmetric strength and knee biomechanics necessary to safely return to activity. We will test the following specific aims:

*AIM 1*: Determine if BFRT improves patient-reported outcomes and lessens the time to return to work or sport following patellar instability.

*Hypothesis:* BFRT will result in significantly improved responses on the patient-reported Norwich Patella Instability, visual analog scale (VAS) for Pain, Cincinnati Occupational Rating Scale, Tegner activity scores, and an earlier return to work and/or sport.

*AIM 2:* Assess whether BFRT results in more symmetric quadriceps strength and knee biomechanics following patellar instability.

*Hypothesis:* BFRT will result in improved quadriceps strength and knee biomechanics (knee moments and excursions).

*AIM 3:* Compare progressive changes in cartilage degradation, muscle architecture, and inflammatory profiles between those treated with or without BFRT over the first 2 years.

*Hypothesis:* BFRT will reduce degradative changes on Magnetic Resonance Imaging (MRI) as well as serum and urinary biomarkers of inflammation and cartilage degradation.

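### Time to return to work or sport is a censored time-to-event outcome, but the plan's only model for its endpoints is repeated measures ANCOVA, which does not fit it

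*Protocol article*

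**What the plan says.** Aim 1 asks whether BFRT improves patient-reported outcomes and "lessens the time to return to work or sport following patellar instability"; its hypothesis includes an earlier return. The Outcome measures section lists "the time to returning to work and/or sporting activities" among the secondary outcomes. The last visit given with that list is at 12 months: "during walking, running, and anterior step-downs 1 week, 9 weeks, 6 months, and 12 months after enrollment".

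The Statistical methods section then gives one model and its reason: "Since all endpoints are quantitative and longitudinal data is collected, repeated measures analysis of covariance (ANCOVAs) will be used". It names two other approaches: MANCOVA for endpoints that are related, and hypothesis tests or logistic regression for categorical variables. On missing data it says "We will not employ imputation methods in the case of missing data".

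The section on randomization, group allocation and blinding adds that participants who discontinue before the final visit, or who become unblinded, are left out of the analysis and replaced.

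**The concern.** The reason given for the model does not hold for an endpoint that the document itself names. A time in months is quantitative, but each person has only one, so there is nothing to model as a repeated measure. For anyone not back at the end of follow-up, all that is known is that the time exceeds their follow-up. ANCOVA has no place for such a value. Transformations and normality checks, which the plan offers as remedies, do not deal with censoring.

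Some non-return is plausible. Clearance for sport depends on six criteria, one of them "90% limb symmetry index as measured with isometric knee extension peak torque and the 60-s step down test". The Background reports that "30% to 50% of those who sustain a primary dislocation experience continued pain and the sensation of instability". The sample size allows for up to 15% loss to follow-up.

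At stake is the return-to-activity part of Aim 1. An analyst who follows the text literally must either leave out people with no return time or give them an arbitrary one. Leaving them out compares speed only among those who succeeded, so it discards the benefit that consists of getting more people back.

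**Working it through.** **The plan's own figure.** There is no sample size or power statement for time to return. The one worked calculation is for the Norwich scale: 2 × (1.96 + 0.84)² × (18.6/13)² ≈ 32.1, so 33 per group. The t-test version gives 33.1, rounded up to the stated 34. That figure reproduces and this point does not touch it.

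**Inputs for the illustration.** From the protocol: 39 per arm enrolled, 34 per arm after loss, last listed visit at 12 months, significance level 0.05 (taken as two-sided). The protocol gives no return rate and no expected effect on return, so the following are assumptions: exponential return times and the medians or return rates shown.

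**Medians 9 versus 6 months (hazard ratio 1.5).** With median m, the rate is λ = ln 2 / m and the share not back by 12 months is S = 2^(−12/m).

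- Sham: S = 2^(−1.333) = 0.397, so 60% return. BFRT: S = 2^(−2) = 0.25, so 75% return.
- Mean time among returners = 1/λ − 12·S/(1 − S). Sham: 12.98 − 7.90 = 5.1 months. BFRT: 8.66 − 4.00 = 4.7 months. Difference: about 0.4 month.
- Mean time with non-returners counted at 12 months (the restricted mean) = (1 − S)/λ. Sham: 0.603 × 12.98 = 7.8. BFRT: 0.75 × 8.66 = 6.5. Difference: 1.3 months. The returners-only comparison keeps about a third of it.
- Simulated power, 39 per arm, 4,000 trials: 7% for a t-test among returners, 31% for log-rank. As a check, expected events are 39 × (0.603 + 0.75) = 52.8. Schoenfeld's formula gives Φ(√(52.8/4) × ln 1.5 − 1.96) = Φ(−0.49), or 31%.

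**Medians 6 versus 4 months.** Means among returners are 4.7 and 5.77 − 1.71 = 4.1, a difference of 0.6 month. Simulated power is 11% against 36%.

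**A wider range.** With 34 per arm, hazard ratio 2.0 and 3,000 simulated trials per row, power was:

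| Sham returned by 12 months | Non-returners dropped | Coded as 12 months | Log-rank |
|---|---|---|---|
| 50% | 9% | 54% | 61% |
| 60% | 14% | 62% | 68% |
| 70% | 22% | 68% | 73% |
| 80% | 34% | 74% | 77% |
| 90% | 52% | 76% | 78% |

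At 70% sham return, dropping shows a gain of 1.0 month against a restricted-mean difference of 2.4 months. At hazard ratio 1.5 over the same return rates, power is 6% to 20% when non-returners are dropped, 21% to 33% when they are coded as 12 months, and 25% to 35% for log-rank. With no true effect, all three analyses rejected in roughly 4% to 6% of trials.

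**The case against.** The strongest reply is that this is loose shorthand in a condensed article. The ANCOVA sentence goes on to speak of differences in scales, and the next paragraph gives methods for categorical variables, so the opening clause cannot be meant literally. A survival model for a secondary outcome is the kind of detail that a full analysis plan supplies. Part of this stands. The clause calls the endpoints quantitative and the data longitudinal; it does not say that every endpoint is a repeated measure. But it does assign a model to all endpoints, and that model is of the wrong class for this one. On the narrow reading, time to return has no stated analysis at all.

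A reader might infer several stronger things that the documents do not support:

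- *That the plan drops non-returners.* It does not say so. A person followed to 12 months without returning has a known status, and the text never calls that missing. Dropping is a likely result of the no-imputation rule, not a stated step.
- *That the better arm could look slower.* This is not shown. With exponential times the mean among returners always falls as the return rate rises, and the faster arm still looked faster in every scenario with an effect.
- *That the model alone stops the trial from answering its return question.* With medians of 9 versus 6 or 6 versus 4 months, log-rank itself has only 31% or 36% power, so sample size is also a limit.
- *That the main results are at risk.* The Norwich scale is the primary variable for Aim 1, and time to return is one of many secondary outcomes.

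**Conclusion.** The point holds for one named secondary outcome: the assigned model does not fit time to return, and nothing else in the text covers it. That much rests on the wording alone.

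The size of the harm depends on what would be done with non-returners and on assumed return rates. If they are dropped, the loss is large when many do not return and smaller, though still present, when 90% of sham participants do. If they are coded as 12 months, it is modest: 2 to 7 percentage points of power at hazard ratio 2.0. The harm is a shrunken estimate and lost power, not false positives. The correction is worth making before the data are unblinded.

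**What to change.** Take time to return out of the ANCOVA sentence and state its analysis:

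- Analyse time to return to sport and time to return to work separately, each with Kaplan-Meier curves and a log-rank test or Cox model stratified by sex, since randomization is by sex.
- Count time from enrolment or randomization (choose one), define the event for each activity, and censor at last contact or 12 months.
- For sport, include all randomized participants. For work, include all randomized participants who were working before injury. Eligibility covers ages 14 to 40 with no employment requirement, and someone without a job is not at risk of returning to one.
- Keep discontinued participants in this analysis as censored, and reconcile that with the rules that exclude and replace discontinued or unblinded participants.
- If only status at visits is recorded, use an interval-censored version. The visible text does not say how return dates are captured.

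The cost is a small amount of standard analysis and, if it is not already recorded, noting the date of return.

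### The repeated measures ANCOVA does not name the outcome's own baseline value as a covariate, although it is collected; this gives up precision and leaves open how the enrolment visit and missed visits are handled

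*Protocol article*

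**What the plan says.** Under Statistical methods, the protocol article names repeated measures ANCOVA for the comparison of BFRT with sham. On covariates it says: "The repeated measures ANCOVAs will adjust for demographic covariates (e.g., age, sex, and race"). The same sentence adds that the analysis will "look for differences across any other potential confounders (such as first-time vs. repeated instability events"). Interactions and transformations are to be explored, and MANCOVA may be used for related endpoints. On missing data: "We will not employ imputation methods in the case of missing data".

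Under Outcome measures, the Norwich scale is "collected at the time of enrollment, 4 weeks, 9 weeks, 6 months, and 12 months after enrollment". That is one baseline and four later assessments, and the urinary biomarkers follow the same schedule. Strength is first measured at 1 week. T1ρ and T2 are measured at 1 week and 12 months only.

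The article does not name the baseline value of the outcome as a covariate. It does not say whether enrolment enters as a covariate or as a repeated level, which model term is the treatment test, or whether the model is a classical complete-case fit or a likelihood-based one.

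**The concern.** In a trial of 78 people, the baseline value of the same measure is usually the most useful covariate available, and here it is collected anyway. The article gives its model, its example covariates and its missing-data rule, so these are stated choices that can be improved. Three things are at stake.

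- **Precision.** Adjusting for demographics but not for baseline leaves outcome variance unexplained that could be removed at almost no cost.
- **The role of the enrolment visit.** If enrolment is one of five repeated levels and the group main effect is the test, the effect is averaged over a visit at which treatment cannot yet have acted.
- **An open model.** Looking for differences across further confounders leaves the adjusted model to be settled once data are seen. In a randomised trial, covariates are better chosen for their prognostic value and fixed in advance.

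A further issue is conditional. A classical repeated measures ANCOVA without imputation needs a complete set of visits, so intermittent misses would reduce the analysed sample.

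**Working it through.** **Inputs from the article (Statistical methods).** SD: "Utilizing the standard deviation of 18.6 points from our pilot results". Target: "13 points difference, effect size = 0.7". Sample: 34 per group for 80% power, 39 enrolled per group. Level: "All analyses will be performed with a significance level of 0.05"; sidedness is not stated, so two-sided is assumed.

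**Assumptions, not in the article.** Correlation r of 0.3, 0.5 or 0.7 between baseline and follow-up, and between any two visits (compound symmetry, equal SD). Missed-visit rate of 3%, 5% or 10%, independent across visits. The effect is a constant 13 points at every post-baseline visit.

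**1. The stated sample size.** 13/18.6 = 0.699. A two-sample t-test needs 33.1 per group for 80% power, rounded up to 34; power at 34 is 0.81. The stated figure reproduces as a comparison of a single score with no baseline term.

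**2. Baseline as a covariate, one visit.** Residual SD = 18.6 × √(1 − r²), 34 per group.

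| r | Residual SD | Power |
|---|---|---|
| none | 18.6 | 0.81 |
| 0.3 | 17.74 | 0.845 |
| 0.5 | 16.11 | 0.906 |
| 0.7 | 13.28 | 0.978 |

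At r = 0.5 this is equivalent to 34/(1 − 0.25) = 45 per group without adjustment.

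**3. Ways of using the enrolment visit, 34 per group.** Variances are in units of 18.6².

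- Enrolment as a fifth level, group main effect: effect 13 × 4/5 = 10.4; variance (1 + 4r)/5, so SD 12.3, 14.4, 16.2.
- Mean of four post-baseline visits, no baseline: effect 13; variance (1 + 3r)/4.
- The same mean adjusted for baseline: effect 13; variance (1 + 3r)/4 − r².
- Post-baseline mean minus enrolment (a group-by-time contrast): effect 13; variance (1 + 3r)/4 + 1 − 2r.

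| Analysis | r = 0.3 | r = 0.5 | r = 0.7 |
|---|---|---|---|
| Enrolment as fifth level, main effect | 0.93 | 0.83 | 0.74 |
| Post-baseline mean, no baseline | 0.985 | 0.949 | 0.897 |
| Change from enrolment | 0.859 | 0.949 | 0.996 |
| Post-baseline mean, baseline-adjusted | 0.996 | 0.996 | >0.999 |

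The baseline-adjusted analysis is at least as good as each alternative at every correlation. The fifth-level main effect is the only one that falls below 80%, and it does so only at the highest correlation.

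**4. Complete cases, if that were the fit.** Participants with all four post-baseline visits, from 39 per arm before any replacement: 39 × (1 − m)⁴. Enrolment is not counted as a visit that can be missed.

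| Miss rate m | Complete per arm | Single-score power |
|---|---|---|
| 3% | 34.5 | 0.82 |
| 5% | 31.8 | 0.78 |
| 10% | 25.6 | 0.69 |

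These powers use the article's single-score basis. For the unadjusted mean of four visits at r = 0.5, the same sample sizes give about 0.95, 0.93 and 0.87.

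**The case against.** The strongest reply is that most of this is inferred from silence in a condensed article. The covariates are introduced as examples and the sentence goes on to other confounders, so a reader who infers that only demographics enter the model goes beyond the text. Baseline is neither named nor excluded, and the statistical analysis plan may name it. This stands, and it limits the point to what should be fixed in advance.

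A reader might also infer that anyone with one missed visit is dropped. No section says so. Declining to impute is compatible with a mixed model that keeps every observed visit. The complete-case figures therefore describe one possible fit, at assumed miss rates. They also leave out the rule under Randomization, group allocation, and blinding that replaces anyone who discontinues before the final visit, with a schedule prepared for 100. With replacement, mainly intermittent misses would erode the sample.

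A third inference is that leaving out baseline biases the result. Under randomisation it does not: it costs precision and leaves chance imbalance unadjusted. The bias risk visible in the article is elsewhere, in the rules that exclude participants who discontinue or become unblinded, which do not fit the intention-to-treat analysis named under Statistical methods.

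Finally, the 80% power claim is not wrong, since it assumes no baseline adjustment. The 10.4-point dilution should not be read alone either: averaging five visits also lowers the SD, and a group-by-time test would use the enrolment value. The article mentions interaction effects only as something to explore, however, and does not say which term is the treatment test.

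**Conclusion.** The point holds as one of efficiency and prespecification. The named model can be bettered at almost no cost by including the baseline value that the trial already collects. At a single visit the gain is from 0.81 to between 0.845 and 0.978 for assumed correlations of 0.3 to 0.7. Testing a group main effect with enrolment as a fifth level would be the poorest choice at correlations of 0.5 and above, and would fall to 0.74 at 0.7. Complete-case fitting would take single-score power below 80% at miss rates of about 5% or more, before replacement.

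All of these sizes rest on correlations and miss rates that the article does not give; the comparisons in step 3 also assume compound symmetry and a constant effect. The conclusion does not depend on one value: baseline adjustment is at least as powerful as the alternatives throughout the range. The documents do not support a claim that the stated sample size is in error, that participants with a missed visit are certain to be removed, or that omitting baseline biases the comparison.

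**What to change.** State in the statistical analysis plan, before unblinding:

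- For outcomes with several post-baseline visits, a likelihood-based mixed model for repeated measures on the post-baseline visits. Terms: baseline value of the outcome, visit, group, group-by-visit, sex (the randomisation stratum), age, and first-time versus recurrent instability. All are fixed in advance and kept whatever imbalance is observed. The treatment contrast to be tested is named.
- All observed visits are used, so a participant with a missed visit still contributes. This is consistent with the decision not to impute.
- For T1ρ and T2, which have one later scan, ANCOVA of the 12-month value on the first scan.
- The 1-week strength and MRI values serve as baseline only if they were taken before the first cuff session.

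The exclusion and replacement rules should be reconciled with intention-to-treat at the same time, because the model can use only the participants those rules leave in.

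The cost is a few degrees of freedom and some wording. No new data, visits or participants are needed.
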